#### Control group

The patients in both the intervention and control groups will receive standard outpatient or inpatient treatment administered by physicians. Outpatient treatment consists of evaluation of psychiatric symptoms, antidepressant pharmacotherapy, and supportive psychotherapy on a bi-weekly or-four-weekly basis. Inpatient treatment consists of sufficient rest for the patient, evaluation of psychiatric symptoms, antidepressant pharmacotherapy, and supportive psychotherapy. All of the participants will receive some case management. Family treatment in the control group consists of one counseling session administered by a nurse. This counseling consists of listening to any issues or problems and providing any information that is ask for. The information requested is usually regarding their communication, relapses, and how to take their drugs. We selected this counseling treatment as the control group’s treatment, because active listening to relatives’ suffering and giving information on recuperation from nurses are within the scope of treatment-as-usual. The one session of counseling by a nurse will last 45 minutes.

#### Therapist training, supervision and fidelity control

Authors FK, NS, and MS were each trained and certified as a family psychoeducation instructor by the JNPF [33]. All staff except one pharmacologist had participated in intensive training which consisted of more than eleven hours using the treatment manual of the JNPF [33]. In order to ensure the fidelity of each session, all sessions will be audiotaped and 25% of each condition will be randomly selected, evaluated, and commented about for improvements continuously by an independent researcher. The counseling session in treatment-as-usual administered by a nurse will also be audiotaped and 20% of each condition will be randomly selected and evaluated by an independent researcher. The raters will each be trained and certified as a family psychoeducation instructor by the JNPF.

### Outcome measure

#### Primary outcome measure of family members - K6

The K6 questionnaire is a six-item self-report questionnaire that was developed to screen for any DSM-IV depressive and anxiety disorders within 30 days prior to its administration and which can also be used to quantify nonspecific psychological distress in general [35]. The participants of this study will not be individuals with a mental disease but will be among the general population, and our previous study showed that the K6 was excellent for measuring changes in the mental health of relatives of MDD patients [36]. K6 has a high screening performance for mood and anxiety disorder, equal to that of the Center for Epidemiologic Studies-Depression Scale (CES-D) [37]. Each item in the K6 questionnaire is rated between 0 = ‘none of the time’ and 4 = ‘all of the time’, and the total score therefore ranges from 0 to 24. Two independent validation studies found the K6 to have an area under the receiver operating characteristic curve between 0.86 and 0.89 in predicting the diagnosis of mental illness based on comprehensive diagnostic interviews [35, 38]. The Japanese version of the K6 questionnaire showed excellent efficacy in screening for anxiety and mood disorders in the Japanese general population, with an area under the receiver operating characteristic curve of 0.94 [39]. The Japanese version of the K10 questionnaire also showed excellent efficacy in screening for anxiety and mood disorders in the Japanese general population, with an area under the receiver operating characteristic curve of 0.94 [39]. In this study, we will use the K6 as it has fewer items than the K10.

#### Secondary outcomes of family members

##### The Japanese version of the Zarit Burden Interview short version (J-ZBI_8)

The Zarit Burden Interview is widely used to assess caregiver burden [40]. The Japanese version of the Zarit Burden Interview (J-ZBI) was developed by Arai *et al*., and the eight-item short version of the J-ZBI (J-ZBI_8) was also developed by Arai *et al*. [41–43]. The items in the J-ZBI_8 are rated on a five-point Likert scale (0 = never to 4 = very often) and the scores on the J-ZBI_8 range from 0 to 32. Cronbach’s α of the J-ZBI_8 was 0.89, and the Pearson’s correlation coefficient between scores on the J-ZBI and J-ZBI_8 was 0.93 [41].

##### The Japanese version of the Family Attitude Scale (FAS)

The FAS, developed by Kavanagh *et al*. [44], is a 30-item self-report instrument and measures families’ EE. The scores for each item are added to give a total score that ranges from 0 to 120, with higher scores indicating higher levels of burden or criticism [44]. A higher FAS rating was significantly correlated with higher levels of criticism (r = 0.44), hostility (r = 0.41), and emotional overinvolvement (EOI) (r = 0.27) in the Camberwell Family Interview (CFI) [45]. The Japanese version of the FAS, developed by Fujita *et al*. [46], showed excellent validity. The relative sensitivity and specificity of EE assessment with the FAS compared with the criticism component of the CFI were 100% and 88.5%, respectively [46].

##### Beck Depression Inventory-II (BDI-II)

BDI-II is a 21-item self-report instrument to assess the existence and severity of symptoms of depression [47]. It has good psychometric properties and acceptability. Each item is rated on a four-point scale ranging from 0 to 3. Studies consistently support the BDI-II as a reliable, internally consistent, and valid scale for assessing depression in psychiatric outpatients and the general population, and in primary care settings [47–49]. The reliability and validity of the Japanese version have been found to be excellent [50].

#### Secondary outcomes in patients

##### Beck depression inventory-II (BDI-II)

We also selected BDI-II as an outcome measure to evaluate the severity of patients’ depressive symptoms.

##### The Medical Outcomes Study 36-item short form health survey (SF-36) version 2

The SF-36 is a self-report questionnaire to assess general quality of life. It contains 36 items that constitute eight measures of physical functioning (PF), role physical (RP), bodily pain (BP), social functioning (SF), general health perceptions (GH), vitality (VT), and mental health (MH). It also provides two summary measures, the physical component summary (PCS) and the mental component summary (MCS). The PCS is associated with PF, RP, BP, GH, and VT. The MCS is associated with MH, RE, SF, VT, and GH. The score of each measure ranges from 0 to 100, and the higher the score, the higher the quality of life. The Japanese version has shown good validity in the general population of Japan [51, 52].

##### The Japanese version of the Family Assessment Device (FAD): J-FAD

The FAD is a 60-item self-report questionnaire developed by Epstein *et al*. [53] to assess the six dimensions of the McMaster Model of Family Functioning as well as the family’s overall level of functioning. The FAD consists of seven subscales: problem solving, communication, roles, affective responsiveness, affective involvement, behavior control, and general functioning. The Japanese version of the FAD was developed by Saeki *et al*. and has shown good validity [54].

### Sample size and statistical power

Sample size was based on a power analysis conducted for the K6 score. Effect sizes were estimated from our previous pilot study [36] (the mean change in the K6 scores pretreatment to post-treatment was 4.9 in 32 relatives of patients with MDD). The change in the K6 scores pretreatment to post-treatment (16 weeks after the randomization) was 4.5 ± 2.5 (mean ± SD) in the family psychoeducation group and 2 ± 2.5 in the control group. With a power of 0.9 to detect a significant difference at *P* = 0.05 (two-sided), it was calculated that 23 patients would be required for each arm. Thus, allowing for a 20% dropout rate, 30 participants would need to be recruited per group.

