## Methods/Design

### Design overview

This randomized controlled trial will be conducted in patients with MDD who will be allocated to one of two arms: family psychoeducation in addition to treatment-as-usual for the patients, and treatment-as-usual. Treatment-as-usual consists of consultation administered by a physician and counseling by a nurse. The primary endpoint is improvement of the mental health of patients’ relatives as measured by K6 scale at 16 weeks (Figure 1). We defined mental health as the state of health of the mind and that when the mental health of relatives was in an unhealthy state, the person suffered from mental disorder such as depressive and anxiety disorder.

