### Participants: inclusion and exclusion criteria

The target population will be patients with MDD lasting more than one year and their relatives (fathers, mothers, husbands, wives, daughters, and sons of patients). Inclusion criteria will be: the patient meets the criteria for MDD according to the DSM-IV (Diagnostic and Statistical Manual of Mental Disorder 4^th^ edn) based on the consensus rating by psychiatrists (who have more than five years’ experience as a physician and more than two years’ experience as a psychiatrist) in charge without using a structured interview; the patient receives antidepressant therapy; the patient had the first episode of MDD more than one year prior; the patient currently fulfills the diagnostic threshold for major depressive episode or partial remission; the patient and their family member(s) are aged between 18 and 85 years; the patient lives with his or her family at the time of participating in this study and is expected to live with his or her family during the investigation period. Exclusion criteria will be: patients who undergo electroconvulsive therapy (ECT) during the investigation period and patients who are at serious suicidal risk.

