### Randomization

Participants will be randomly allocated to one of the two groups with equal probability. This random assignment will be made in a 1:1 ratio. An independent statistician will generate the random allocation sequences by a computer using minimization [30], and stratify the relatives according to the severity of mental state (K6 score of 5 or more, or less than 5). Allocation sequences will be kept centrally and the allocation will be provided by facsimile to us. The randomization schedule is not available to anyone except the statistician.

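### The unit of allocation, stratification and sample size shifts between patient, participant and relative, although a patient may bring several relatives whose K6 scores are correlated

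*Protocol article*

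**What the plan says.** All references are to the Protocol article.

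- **Abstract, Methods/Design:** participants are both the patients and their relatives, and the trial is individually randomized.
- **Design overview:** the patient is allocated: "This randomized controlled trial will be conducted in patients with MDD who will be allocated to one of two arms". The primary endpoint in the same section is the relatives' K6 at 16 weeks.
- **Randomization:** participants are allocated 1:1 by minimization, but the statistician will "stratify the relatives according to the severity of mental state", with the K6 cut between 4 and 5.
- **Participants: inclusion and exclusion criteria:** more than one relative per patient is possible: "the patient and their family member(s) are aged between 18 and 85 years". Parents, spouses and children are all eligible. No section sets a limit of one or names an index relative.
- **Sample size and statistical power:** the pilot change comes from 32 relatives. The assumed K6 changes are "4.5 ± 2.5 (mean ± SD) in the family psychoeducation group and 2 ± 2.5 in the control group". The result is that "it was calculated that 23 patients would be required for each arm", and after 20% dropout "30 participants would need to be recruited per group".
- **Statistical analysis:** analysis of covariance at 16 weeks if no data are missing, otherwise a maximum likelihood mixed model. Neither is given a family term, and missing data are the only trigger for the mixed model.

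**The concern.** One sample size paragraph uses three units: relatives for the pilot, patients for the required number, participants for the target. These agree only if each patient contributes exactly one relative. The protocol does not say so, and its eligibility wording allows more.

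Relatives in one household share the patient and the home, so their K6 changes are likely to be correlated. Two things follow if several per patient are enrolled. First, an analysis that treats each relative as independent has too small a standard error, so the primary test rejects too often. Second, stratification on the relative's K6 is not defined for a family in which one relative scores 5 or more and another scores less than 5, while the design overview allocates that family through its one patient. The unit also decides whether the planned number is adequate: 30 families and 30 relatives per arm are different trials.

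**Working it through.** **Inputs from the protocol (Sample size and statistical power).** Changes of 4.5 and 2.0, SD 2.5, so difference 2.5 and standardised difference d = 2.5/2.5 = 1.0; two-sided 5% level; power 0.90; dropout 20%.

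**Step 1: reproduce the stated figures.** The normal approximation is n = 2 × [(1.96 + 1.28) × 2.5/2.5]² = 21.0, rounded up to 22 per arm. The exact two-sample t-test has power 0.8997 at 22 and 0.9125 at 23, so 23 per arm is right. Dropout: 23/(1 − 0.20) = 28.75, or 29; the stated 30 is a small rounding up and leaves 30 × 0.8 = 24 completers, with power 0.92. The arithmetic is sound for independent observations and contains no design effect.

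**Step 2: inputs that the protocol does not give (assumptions).** Relatives per family, m, and within-family intraclass correlation of the K6 change, ICC. For the main illustration m = 30/16 = 1.875 (about 1.9). The 16 is an inference, not a stated total: the section Multifamily psychoeducation mentions four groups of the relatives of about four patients, and 4 × 4 = 16. ICC is taken as 0.2 and 0.4. The wider range is m = 1.2 to 3 and ICC = 0.1 to 0.5.

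**Step 3: design effect.** DE = 1 + (m − 1) × ICC.

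- ICC 0.2: DE = 1 + 0.875 × 0.2 = 1.175.
- ICC 0.4: DE = 1 + 0.875 × 0.4 = 1.35.
- Wider range: 1 + 0.2 × 0.1 = 1.02 up to 1 + 2 × 0.5 = 2.0.

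**Step 4: type I error if relatives are analysed as independent.** Actual level = 2 × [1 − Φ(1.96/√DE)].

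- ICC 0.2: 1.96/√1.175 = 1.81, level 7.1%.
- ICC 0.4: 1.96/√1.35 = 1.69, level 9.2%.
- Wider range: 5.2% at DE 1.02, 16.6% at DE 2.0.

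This depends on DE alone, so it applies whether 23 and 30 count families or relatives.

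**Step 5: power, with the correlation properly modelled.** Effective n = relatives per arm/DE; t-test at d = 1.0.

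| Reading of the target, at 24 completing units per arm | ICC | Relatives per arm | Effective n | Power |
|---|---|---|---|---|
| One relative per patient | n/a | 24 | 24 | 0.92 |
| 24 are relatives, 1.875 per family | 0.2 | 24 | 24/1.175 = 20.4 | 0.88 |
| 24 are relatives, 1.875 per family | 0.4 | 24 | 24/1.35 = 17.8 | 0.83 |
| 24 are families, 1.875 relatives each | 0.2 | 45 | 45/1.175 = 38.3 | 0.99 |
| 24 are families, 1.875 relatives each | 0.4 | 45 | 45/1.35 = 33.3 | 0.98 |

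So power is at risk only when the target counts relatives.

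**Step 6: stratum conflict.** This needs no arithmetic. A patient who joins with two relatives, one with K6 of 3 and one with K6 of 8, has a relative in each stratum, and the protocol does not say which score enters the minimization.

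**The case against.** The strongest defence is that the text is loose, not faulty. Most of it treats the patient as the unit with the family following: Procedure gives the ID number to the patient, and Control group speaks of patients in both arms. Stratifying the relatives can be read as one relative for each patient. The plural in the age criterion permits several relatives without saying that several will be scored, and with one each, 23 and 30 hold exactly. An article may also leave a family term to a fuller document.

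Much of this stands, and it limits the point in four ways.

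- A reader might infer that the analysis section also switches unit. It does not: it names no unit. The inconsistency is in allocation, stratification and sample size. The type I error figures are therefore conditional on an analysis that ignores family, which the protocol neither states outright nor excludes.
- A reader might infer that relatives of one patient could be sent to different arms. That is speculative, since the text mainly allocates the patient.
- A reader might infer that the trial is underpowered. The sentence quoted on sample size says patients; taken literally, extra relatives raise power. The loss needs the target to mean relatives, and the 1.9 per family rests on the inferred 16 families. The sentence behind it may mean something else, and 16 is below the 23 required per arm.
- A reader might infer that the SD of 2.5 is wrong when families supply several relatives. A between-person SD does not depend on that number.

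What the defence does not remove is that the stated units disagree, that nothing limits a patient to one relative, and that the stratum is undefined when there are two.

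**Conclusion.** The point holds as an inconsistency in the stated unit, not as an arithmetic error. If one relative per patient is enrolled or analysed, the required number and the target stand. If several are analysed as independent, the primary test runs at about 7% to 9% instead of 5% under 1.9 relatives per family and ICC 0.2 to 0.4, and at about 5% to 17% over the wider range. If, in addition, the target counts relatives, power at 24 completers is about 0.88 to 0.83 against the planned 0.90 under the same main assumptions. Family size and ICC are assumptions throughout; the protocol gives neither. The stratum conflict follows from the text once a patient has two relatives. Because the unit sets both the denominator and the error rate of the primary test, it should be settled before unblinded analysis.

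**What to change.** 1. **Randomization:** state that each patient-family is randomised once, and that its stratum is the baseline K6 of one index relative named before randomisation.
2. **Sample size:** restate 23 and 30 per arm as families.
3. **Statistical analysis:** run the primary analysis on the index relative, or on all enrolled relatives with a family random intercept, whether or not data are missing. Choose one in advance.
4. **Families already randomised:** Trial status reports that recruitment began in October 2012. For these families, define the index relative by a rule that uses baseline data only, fixed before unblinded analysis.

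The cost is a few sentences in three sections and one extra field on the baseline form. If 30 families per arm is what was intended, recruitment does not change.

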### Statistical analysis

Statistical analyses will be performed using SPSS 19 J for Windows. Descriptive data analysis will be conducted by calculating mean scores and standard deviation. All analyses will be based on the intent-to-treat model. We will use analysis of covariance at 16 weeks if there is no missing data at that time. If missing data is observed, we will use the maximum likelihood mixed model which accounts for missing data, provided that the data are missing at random, conditional on the covariates and the baseline values of the outcome. *P* <0.05 will be set to test the null hypothesis.

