### Treatment

#### Multifamily psychoeducation

The family intervention program, which we call ‘multifamily psychoeducation’, is based on the McFarlane Model [31], the Evidence-Based Practices Toolkit for Family Psycho-Education [32], and the standard model of the Japanese Network of Psychoeducation and Family Support Program (JNPF) [33]. The multifamily psychoeducational program will consist of four sessions. Each of the four multifamily psychoeducational program groups will consist of the relatives of approximately four patients. The staff will consist of one or two psychiatrists, one or two nurses, one pharmacologist, and one social worker. The teaching materials for the relatives of the patients are a videotape produced by the Department of Neuropsychiatry, Kochi Medical School [34], including the videotaped interview of the experience of a patient with MDD, an explanation of the cause of MDD using computer graphics images of synapses and neurotransmitters, and a booklet developed by our department. At the first session we will give the participants information on the causes and symptoms of major depression, at the second session we will provide information on drug treatment, at the third session we will provide information on community resources, and at the fourth session we will provide guidelines for families caring for patients. After the lecture in each session, we will provide supportive group therapy focusing on problem-solving skills for approximately 90 minutes. In the group therapy sessions, the participants will be encouraged to give a narrative of their subjective experience in taking care of the MDD patient. Each session will last approximately two hours. The groups will meet once every two weeks over the course of six weeks.

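### Psychoeducation is delivered in therapy groups of about four families, but neither the sample size nor the stated primary analysis allows for clustering in that one arm

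*Protocol article*

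**What the plan says.** **Delivery.** The section Multifamily psychoeducation states that "Each of the four multifamily psychoeducational program groups will consist of the relatives of approximately four patients". There are four sessions of about two hours, and after each lecture "we will provide supportive group therapy focusing on problem-solving skills for approximately 90 minutes". Under Control group, family treatment is one 45-minute counselling session with a nurse, and no group is described. The abstract says that randomisation is by individual.

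**Sample size.** Under Sample size and statistical power, the change in K6 "was 4.5 ± 2.5 (mean ± SD) in the family psychoeducation group" and "2 ± 2.5 in the control group". For power 0.9 at two-sided 0.05, "it was calculated that 23 patients would be required for each arm". Then, "allowing for a 20% dropout rate, 30 participants would need to be recruited per group". No ICC or design effect appears.

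**Analysis.** Under Statistical analysis, "We will use analysis of covariance at 16 weeks if there is no missing data at that time". If data are missing, a maximum likelihood mixed model is used, justified by a missing-at-random assumption. Neither model is given a term for therapy group.

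**The concern.** This is a partially nested design: individuals are randomised, one arm is then treated in groups, and the other is not. About three quarters of each session (90 of 120 minutes) is spent in joint problem-solving, and the Discussion presents relatives sharing experiences and advising one another as a feature of the programme. Some correlation of K6 within a group is therefore to be expected.

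With a positive ICC, the mean of the psychoeducation arm varies more than independent observations would. A test that omits the group has confidence intervals that are too narrow and a p-value that is on average too small. This affects the test of the trial's only stated hypothesis. With roughly four to six groups, one or two unusually successful groups could produce a positive result, and the stated analysis would not show it.

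**Working it through.** **1. Reproduce the plan's figure.** Inputs from Sample size and statistical power: difference 4.5 − 2 = 2.5, SD 2.5, so the standardised effect is 1.0; two-sided 0.05; power 0.9. The two-sample t-test (noncentral t) gives power 0.8997 at 22 per arm and 0.912 at 23. The stated 23 is thus exactly the figure for independent observations. Allowing for dropout, 23 / 0.8 = 28.75, i.e. 29, which the article rounds to 30. Thirty recruited less 20% leaves 24 per arm, with power 0.924 under independence.

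**2. Clustering in one arm.** Let *m* be the group size and *k* the number of groups. The design effect in the psychoeducation arm is DEFF = 1 + (*m* − 1) × ICC, and in the control arm it is 1. With equal arms, the true variance of the difference is (DEFF + 1)/2 times the variance that the unadjusted test assumes. The ICC is not in the article, so 0.05 to 0.20 is assumed.

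**3. Type I error of the unadjusted test.** The approximation is 2 × [1 − Φ(1.96 / √((DEFF + 1)/2))]. It was checked by simulation, with agreement to within about 0.2 percentage points.

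| Groups | ICC | DEFF | Variance ratio | Type I error |
|---|---|---|---|---|
| six of four | 0.05 | 1.15 | 1.075 | 5.9% |
| six of four | 0.10 | 1.30 | 1.15 | 6.8% |
| six of four | 0.20 | 1.60 | 1.30 | 8.6% |
| four of six | 0.05 | 1.25 | 1.125 | 6.5% |
| four of six | 0.10 | 1.50 | 1.25 | 8.0% |
| four of six | 0.20 | 2.00 | 1.50 | 11.0% |

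The second layout is shown because the article speaks of four groups. Four groups of about four patients cover only 16 families; to hold 24 completers, four groups would need six each.

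**4. Power of a valid test of change scores.** Six groups of four against 24 controls, effect 1.0, with Satterthwaite degrees of freedom based on the number of groups: 0.877, 0.851 and 0.797 at ICC 0.05, 0.10 and 0.20. Simulation of a Welch test that uses group means in the psychoeducation arm gives about 0.87, 0.845 and 0.79. Without the loss of degrees of freedom, the figures are 0.905, 0.885 and 0.845.

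**5. Gain from baseline adjustment.** The SD of 2.5 is that of a change score, but the stated analysis is ANCOVA. If baseline and 16-week variances are equal and their correlation is *r*, the ANCOVA variance is (1 + *r*)/2 times the change-score variance. The article gives no *r*. Applying this factor to the Satterthwaite calculation, with the ICC assumed unchanged by adjustment:

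| Assumed *r* | ICC 0.05 | ICC 0.10 | ICC 0.20 |
|---|---|---|---|
| 0.5 | 0.950 | 0.933 | 0.896 |
| 0.7 | 0.923 | 0.902 | 0.857 |

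Under the same assumption, baseline adjustment scales both the true and the assumed variance, so it does not remove the type I inflation in step 3.

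**The case against.** **The effect is conditional.** No ICC is given, and at zero nothing is lost. At 0.05 with groups of four, the type I error is about 6%, and the rounding up to 30 recruits keeps power at 0.905 before any loss of degrees of freedom. This stands: the point must be stated over a range.

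**The power loss is not shown.** A reader might infer that the stated 0.9 power is not delivered. The article does not support that. Power for the planned ANCOVA can be at or above 0.9 even with clustering, depending on a baseline correlation that is also not given. This stands too.

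**Larger groups.** A reader might also suppose two relatives per patient, hence three groups of eight, and a much larger loss. The sample size is expressed as patients per arm and the groups are sized by patients. Two relatives for each of 24 patients would be six groups and 48 relatives; three groups of eight would mean only 12 patients. The article does use the word participants for the 30, so the unit is not perfectly clear, but that scenario halves the patients and should not be relied on.

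**Silence is not exclusion.** The analysis section is one paragraph, and random effects are often left to an analysis plan, which is not shown. This stands in part. An analysis plan could add a group term. However, the article names the primary model, introduces the mixed model only for missing data, and fixes a sample size that no later model term can make allow for clustering.

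**Conclusion.** The point holds in conditional form, and should be fixed. The article fixes group delivery in one arm, a sample size that assumes independence, and a primary analysis with no stated group term. For any positive ICC, that analysis gives an interval that is too narrow. Over an assumed ICC of 0.05 to 0.20, type I error is about 6% to 8.5% with six groups of four, and about 6.5% to 11% with four groups of six, instead of 5%.

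On power, a group-adjusted test of change scores gives about 0.87 to 0.79 over the same range, and about 0.95 to 0.89 with ANCOVA at a baseline correlation of 0.5. A shortfall is possible but not established. These figures rest on 24 evaluable relatives per arm, one per patient, equal group sizes and the planned effect of 1.0.

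**What to change.** 1. Record a therapy-group identifier for every relative in the psychoeducation arm.
2. Make the primary analysis a mixed model for K6 at 16 weeks, with baseline K6 as covariate, a random therapy-group effect in the psychoeducation arm only (each control treated as a group of one), and Satterthwaite or equivalent small-sample degrees of freedom. Use it whether or not data are missing.
3. Restate power at 30 recruited per arm over an ICC of 0.05 to 0.20, giving the assumed baseline correlation and the expected number and size of groups.

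The cost is one recorded variable and revised wording. Confidence intervals become slightly wider and the stated power may be less favourable. No extra patients are required. The article reports that recruitment is still under way, so the change can be made before outcomes are complete.

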**Methods/Design:**

Participants are patients with MDD lasting more than one year and their relatives. Individually randomized, parallel-group trial design will be employed. Participants will be allocated to one of two treatment conditions: relatives will receive (a) family psychoeducation (four, two-hour biweekly multifamily psychoeducation sessions) plus treatment-as-usual for the patient (consultation by physicians), or (b) counseling for the family (one counseling session from a nurse) plus treatment-as-usual for the patient. The primary outcome measure will be relatives’ mental health as measured by K6 that was developed to screen for DSM-IV depressive and anxiety disorder. Additionally, the severity of depressive symptoms in patients measured by the Beck Depression Inventory–II (BDI-II) scale will be assessed. Data from the intention-to-treat sample will be analyzed 16 weeks after randomization.

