### Aims

In the present study, we perform a randomized controlled trial to examine the effectiveness of family psychoeducation in improving the mental health of the relatives of patients with MDD lasting more than one year. The hypothesis is that, compared with relatives who receive one regular counseling session from a nurse, relatives receiving family psychoeducation will show a greater improvement in mental health as measured by K6 scale at 16 weeks post-randomization.

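### The primary method switches on any missing 16-week value; the mixed model that will in practice be used should be the single named primary analysis, fitted by REML with its 16-week contrast stated

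*Protocol article*

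**What the plan says.** The endpoint is fixed in three places. The Aims state the hypothesis as a "greater improvement in mental health as measured by K6 scale at 16 weeks post-randomization". The Design overview says: "The primary endpoint is improvement of the mental health of patients’ relatives as measured by K6 scale at 16 weeks". The abstract says: "Data from the intention-to-treat sample will be analyzed 16 weeks after randomization".

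The Statistical analysis section then gives a two-branch rule. First branch: "We will use analysis of covariance at 16 weeks if there is no missing data at that time". Second branch: "If missing data is observed, we will use the maximum likelihood mixed model which accounts for missing data". The second branch is qualified by a missing-at-random assumption given baseline scores and covariates that are not named. The first sentence names the time point. The second names neither a time point nor a contrast.

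The Procedure section lists assessments at baseline and at 8, 16 and 32 (the unit is missing in the text; weeks are assumed here). The Sample size section arrives at 30 per group, "allowing for a 20% dropout rate".

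**The concern.** Three things follow from the rule as written.

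1. A single missing 16-week value changes the primary method. This is a stated rule, so it is not a detail left for a later analysis plan to supply.
2. The branch written as the fallback is the one that will be used, and it is the less specified of the two. With follow-up visits at 8, 16 and 32, a repeated-measures mixed model can yield an overall arm effect, a slope or a contrast at one visit. The sentence does not say which of these is the primary test. The sample size was calculated for the 16-week change.
3. The model is described as maximum likelihood. Taken literally, full ML does not correct the variance estimate for the fixed effects fitted, and in a trial of about 50 evaluable relatives that shortfall is visible.

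At stake are a clear link between the powered hypothesis and the tested quantity, and a small excess over the nominal error rate.

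**Working it through.** **Inputs.** From Sample size and statistical power: K6 change 4.5 versus 2, SD 2.5 in each group, two-sided 0.05, power 0.9, 23 per arm evaluable, 20% dropout, 30 per arm recruited (60 in all). From Procedure: follow-up at 8, 16 and 32.

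**The plan's own sample size.** The difference is 4.5 − 2 = 2.5, so the standardised effect is 2.5/2.5 = 1.0. A two-sample t-test needs 22.02 per arm, rounded up to 23, with power 0.912 at 23. Inflating for dropout, 23/0.8 = 28.75, or 29, against 30 stated. The figures reproduce.

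**How often the ANCOVA branch would apply.** With independent dropout at rate d, P(no missing 16-week value among 60) = (1 − d)^60.

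| Missing at 16 weeks | P(ANCOVA branch) |
|---|---|
| 20% (plan) | 0.0000015 |
| 10% (assumed) | 0.0018 |
| 5% (assumed) | 0.046 |
| 2% (assumed) | 0.30 |
| 1% (assumed) | 0.55 |

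At the plan's own rate the first branch is effectively never reached.

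**What an unspecified contrast could change (illustration with assumed profiles).** If the planned difference of 2.5 holds at 8 and 16 but is gone at 32, the effect averaged over visits is (2.5 + 2.5 + 0)/3 = 1.67. If half remains at 32, it is (2.5 + 2.5 + 1.25)/3 = 2.08. Either is smaller than the 2.5 used for the sample size. These figures show only that the contrast matters. They do not show that the plan intends an average.

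**Literal full ML.** For one time point with n relatives and p fixed effects, the ML residual variance is (n − p)/n times the unbiased one. Rejecting when the ML-based statistic exceeds t(0.975, n − p) is the same as rejecting when the correct t exceeds t(0.975, n − p) × √((n − p)/n).

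| n | p | Variance ratio | SE ratio | Effective cut-off | True two-sided error |
|---|---|---|---|---|---|
| 46 | 3 | 0.935 | 0.967 | 1.950 | 0.058 |
| 46 | 4 | 0.913 | 0.956 | 1.928 | 0.061 |
| 48 | 3 | 0.938 | 0.968 | 1.950 | 0.057 |
| 48 | 4 | 0.917 | 0.957 | 1.930 | 0.060 |
| 60 | 3 | 0.950 | 0.975 | 1.952 | 0.056 |
| 60 | 4 | 0.933 | 0.966 | 1.935 | 0.058 |

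Here 46 is 2 × 23, 48 is 60 × 0.8, and 60 is everyone randomised. The range is about 0.056 to 0.061. The formula is cross-sectional, so for a repeated-measures fit it is only an approximation.

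**Stratum.** A simulation of ANCOVA under assumed inputs (baseline K6 mean 6, SD 4, slope 0.6, residual SD 2.5, 20% random dropout, 5,000 runs) gave type I error 0.051 with baseline K6 alone and 0.051 with the K6 stratum added. Power was 0.916 and 0.911.

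**The case against.** The best defence is that the rule does little harm. Its trigger is objective, set in advance and unrelated to the observed treatment effect. Since the ANCOVA branch is almost never reached, the plan in effect has one model and little analytic freedom. This stands: the switch has little numerical consequence. It also means that the switch serves no purpose.

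A second defence is that the 16-week target is clear from the rest of the article, and that the exact contrast, covariates and degrees of freedom commonly sit in an analysis plan. This largely stands too. A reader might infer that neither model is tied to 16 weeks, or that the trial will test a slope or an overall effect. The documents do not support either inference: the ANCOVA is expressly at 16 weeks, and the abstract, Aims and Design overview fix the endpoint there. What remains is that the sentence describing the model that will actually be used does not itself carry the time point.

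Third, maximum likelihood may be a loose label that includes REML. The text does not exclude this, so the error figures hold only on the literal reading.

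A reader might also object that the allocation factor is left out of the model, since the Randomization section says the statistician will "stratify the relatives according to the severity of mental state (K6 score of 5 or more, or less than 5". It is not named, but the covariates are unnamed altogether, so its absence is not established. The factor is a cut of baseline K6, and the simulation shows a negligible effect once baseline K6 is included. A further worry, about a poorly estimated therapy-group variance, has no footing here because the article describes no such component.

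**Conclusion.** The point holds in a limited form. The protocol article makes the primary method depend on whether any 16-week value is missing. At its own 20% dropout among 60, with independent dropout, the mixed model is in practice the primary analysis: the alternative has a chance of about 1.5 in a million. That model's sentence lacks the 16-week time point set elsewhere for the primary endpoint. On a literal reading, full ML raises a nominal 0.05 to about 0.056 to 0.061, given 46 to 60 relatives, 3 or 4 fixed effects and the single-time-point approximation.

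No biased estimate, wrong sample size or material inflation from the switch itself has been shown, and none should be inferred. This is a better method available at no cost, not a flaw that invalidates the analysis.

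**What to change.** Replace the two-branch rule with one primary model, used whatever the missingness: a REML mixed model for repeated measures in all randomised relatives, with arm, visit, arm × visit and baseline K6, and Satterthwaite degrees of freedom. State that the primary test is the arm contrast at 16 weeks. Keep ANCOVA on observed 16-week data as a sensitivity analysis. Adding the K6 stratum is optional.

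The cost is about two sentences of analysis wording. No new data are needed, and the sample size stays at 23 evaluable and 30 recruited per arm. The article reports the trial as still recruiting, so at that stage the change can be made before any analysis.
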